# **Limitations of the study**

In this study, the participants will be enrolled from OPD basis, so, we cannot resolve the adherence of dietary advice to all participants. Similarly, there may be a recall bias to collect 24-hour dietary recall and may have social desirability bias for collecting behavioral related history. To minimize recall bias, proper probing will be carried out. Likewise, interviewer bias can occur, to minimize it the length of time taken to interview the average intervention and the average control will be noted. Selection bias can occur during the selection process. We will strongly follow randomization to the selection of intervention and usual care arms by a trained data enumerator so that this will minimize the confounding. Also, the cross-contamination may occur between intervention and control arms. We will suggest the participants from the intervention arm not to share the provided information with the others to prevent cross contamination.

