## **7.2. Types of study**

a. Experimental/Interventional: The proposed study is a randomized, controlled, open-label trial to evaluate the effectiveness of dietitian-led dietary approach to management of diabetes on reduction of HbA1c level and macronutrient intake among T2DM patients in tertiary care hospital in Kathmandu, Nepal (Figure 2). This study utilized two-arm RCT with equal allocation of participants between the intervention and control group/usual care arm. The intervention will include a dietitian-led nutrition education, counseling session and individual basis diet plan emphasis on glycemic control diet targeted to T2DM patients attending during the OPD visits in hospital.

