## **7.12. In case of RCT, process of randomization and blinding, description of stopping rules for individuals for part of the study or entire study, the procedures and conditions for breaking the codes etc.**

The dietitians and enumerators will explain the purpose of the study to the participants and those participants who willing to give written informed consent and meet the inclusion criteria will be randomly assigned to either the intervention or the usual care arm. Once participants sign an informed written consent form, he or she will be enrolled in the study. Eventually, participants will be enrolled in either intervention or control groups randomly using computer generated random numbers.

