**Data collation phase**

- Firstly, thesis writing students will be trained for data collection procedure, participants’ selection and randomization. The manual of data collection will be developed and distributed to the enumerators and study team members. Conduct a week-long training workshop to the data enumerators and dietitian regarding data collection techniques and diet counseling. The study questionnaire, anthropometric instruments, biochemical instruments will be pre-tested. Pre-testing should be conducted in order to maintain the accuracy and clarity of tools.
- Nutritional counseling and diet plan guidelines will be pre-tested in another hospital not included in the study area. Pre-tested guidelines will be approved by a multi-disciplinary expert team.
- After pre-testing all the ambiguous, misleading and wrongly interpreted questions will be omitted and the questionnaire will be revised in accordance with the findings of pre-testing. Instruments such as biochemical tools and clinical tools will be regularly calibrated before use.
- Supervision and monitoring during the data collection will be done by the investigators.
- Confidentiality while taking the interview will be maintained in order to avoid bias.
- The core study team will be made responsible to maintain the appropriateness of sampling and data collection techniques. Interviews will be conducted into the local language and the responses will be coded simultaneously on the questionnaire. The filled-in questionnaire will be checked and edited each day by the supervisor at the data collection sites.
- The data collection will be carried out in close supervision of the research team. In order to maintain the quality of the data collection, the investigators will make at least 10% accompaniments and 20% back checks every day. Any error in data collection will be recorded in the investigator logbook and the enumerators will be informed of the errors and suggested the improvement measures.
- All the filled-up questionnaires will be safely stored in a locker.

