# **Work plan**

| **Gantt chart** | | | | | | | | | | | | | | | |
| --- | --- | --- | --- | --- | --- | --- | --- | --- | --- | --- | --- | --- | --- | --- | --- |
| S.N | Activities | **2019 A.D** | | **2020 A.D.** | | | **2021 AD** | | | | | | | | |
|  |  | **Nov** | **Dec** |  | | | **Jan** | **Feb** | **March** | **April** | **May** | **June** | **July** | **Sept** | **Oct** |
| 1 | Drafting proposal | **×** |  |  |  |  |  |  |  |  |  |  |  |  |  |
| 2 | Proposal submitted to UGC and under review |  | **×** | **×** | **×** |  |  |  |  |  |  |  |  |  |  |
| 3 | Submission and approve proposal to NHRC |  |  |  | **×** | **×** |  |  |  |  |  |  |  |  |  |
| 4 | Tools development |  |  |  |  | **×** |  |  |  |  |  |  |  |  |  |
| 5 | Nutrition counselling and diet plan guidelines developed. |  |  |  |  |  | **×** |  |  |  |  |  |  |  |  |
| 6 | Orientation to stakeholders  And guidelines approval |  |  |  |  |  | **×** |  |  |  |  |  |  |  |  |
| 7 | Training of thesis writing students |  |  |  |  |  | **×** |  |  |  |  |  |  |  |  |
| 8 | Sampling framework |  |  |  |  |  |  | **×** |  |  |  |  |  |  |  |
| 9 | Finalization of intervention and usual care arms in target hospital |  |  |  |  |  |  | **×** |  |  |  |  |  |  |  |
| 10 | Tools pre-testing and finalization |  |  |  |  |  |  | **×** |  |  |  |  |  |  |  |
| 11 | Finalization of research participants |  |  |  |  |  |  |  | **×** |  |  |  |  |  |  |
|  | Baseline data collection |  |  |  |  |  |  |  |  | **×** |  |  |  |  |  |
| 12 | Intervention |  |  |  |  |  |  |  |  |  | **×** | **×** | **×** |  |  |
| 13 | Midline data collection |  |  |  |  |  |  |  |  |  | **×** | **×** | **×** |  |  |
| 14 | Midline data analysis |  |  |  |  |  |  |  |  |  |  |  | **×** |  |  |
| 15 | Endline data collection |  |  |  |  |  |  |  |  |  |  |  | **×** |  |  |
| 16 | Endline data analysis |  |  |  |  |  |  |  |  |  |  |  | **×** |  |  |
| 17 | Literature review |  |  |  |  |  |  |  |  |  |  |  |  | **×** |  |
| 18 | Report writing |  |  |  |  |  |  |  |  |  |  |  |  |  | **×** |
| 19 | Dissemination of report |  |  |  |  |  |  |  |  |  |  |  |  |  | **×** |

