# **Budget**

| **Proposed Budget for the study** | | | | | | | **Justifications** |
| --- | --- | --- | --- | --- | --- | --- | --- |
| **S.N.** | **Description** | **Person** | **Months** | **LOE (%)** | **Rate NRs.** | **Total Amount (NRs.)** |  |
| **A** | **Personal Cost** |  |  |  |  |  |  |
| A1 | Principal Investigator | 1 | 14 | 0.3 | 2,500 | 10,500 | Since both principal investigator and Co-Investigators are full-time faculty at Asian College for Advance Studies, we have allocated minimum cost that includes minimum allowances to cover their necessary expenses. |
| A2 | Co-Investigator | 1 | 14 | 0.3 | 2,500 | 10,500 |  |
| A3 | Thesis writing students | 2 | 3 | 0.5 | 4,000 | 10,000 | This cost covers the minimum remuneration for thesis writing students who will involve in this study and work as an enumerators |
| A4 | Dietitian fee | 1 | 3 | 0.5 | 4,000 | 6,000 | Dietitian will be provided with a minimum fee for the patients counseling and diet plan to the study participants |
|  | **Sub-total** |  |  |  |  | **37,000** |  |
| **B** | **Laboratory cost** | **Person Items** | **Unit** |  | **Unit Cost** | **Total Amount** |  |
| B.1 | Bio-chemical test (testing service cost) | 156 | 2 |  | 600 | 202,800 | This cost covers the Biochemical tests charge during baseline, midline and end line. |
| B2 | Stadiometer | 2 | 1 | 1 |  |  | This equipment will be provided by Asian College For Advance Studies |
| B3 | Weighing Machine | 2 | 1 | 1 |  |  | This equipment will be provided by Asian College For Advance Studies |
| B4 | BP Set | 2 | 1 | 1 | 2,500 | 5,000 | This equipment will be provided by Asian College For Advance Studies |
|  | **Sub-total** |  |  |  |  | **207,800** |  |
| **C** | **Field Cost** | **Person** | **Days** | **Times** | **Unit Cost** | **Total Amount** |  |
| C1 | Travel cost | 2 | 72 | 1 | 100 | 14,400 | This cost is allocated for enumerator travel costs during the data collection period. |
| C2 | Daily allowances | 1 | 72 | 1 | 200 | 14,400 | Daily allowances for enumerators during the data collection period |
| C3 | Survey cost (tools pretesting) | 1 | 1 | 1 | 20,000 | 20,000 | Cost for tools pre-testing (Data collection tools, IEC materials, and menu plan sheet pre-testing ) |
|  | **Sub-total** |  |  |  |  | **48,000** |  |
| **D** | **Office cost** | **Event** | **Days** | **Times** | **Unit Cost** | **Total Amount** |  |

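### Randomisation is given to the enumerator role that also approaches patients and takes measurements, with no concealment step, no independent list holder and no rule that baseline precedes assignment

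*Protocol*

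**What the plan says.** Four parts of the protocol bear on who assigns patients and when.

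- **Recruitment (section 7.12).** "The dietitians and enumerators will explain the purpose of the study to the participants". The Informed consent section likewise has the enumerator explain purpose, benefits and harms.
- **Assignment (Limitations of the study; Data collation phase).** "We will strongly follow randomization to the selection of intervention and usual care arms by a trained data enumerator". In training, "thesis writing students will be trained for data collection procedure, participants’ selection and randomization". The Budget identifies these students as the enumerators: it pays for "thesis writing students who will involve in this study and work as an enumerators".
- **Method (section 7.12).** After consent, "participants will be enrolled in either intervention or control groups randomly using computer generated random numbers". Nothing further is said about how the sequence is made, held or released.
- **Measurement (section 7.10, Tools and procedure).** The trained enumerator takes the physical measurements. The Data collation phase adds that enumerators are given the data collection manual, trained in data collection techniques and told of errors found in their data collection.

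The Biases and Limitations sections both name selection bias as a risk, and both offer close adherence to randomisation as the remedy.

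**The concern.** Randomisation protects a comparison only if the person deciding whether a patient enters cannot know or influence the next assignment. Here one role approaches the patient, assigns the arm and takes measurements, and the trial is open label. If that role can see the next number, a patient expected to do well or badly can be steered towards or away from an arm: by how the study is explained, by a judgement on eligibility, or by deferring the approach. Eligibility leaves room for this, because the exclusion for severe illness in section 7.7 has no definition.

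Intention-to-treat analysis does not repair such selection, since it preserves the groups as they were formed. Adjustment for recorded baseline variables removes only what those variables capture. A second, separate risk is that baseline interviews may be held once interviewer or patient knows the arm.

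**Working it through.** There is no planned figure to reproduce and no arithmetic that settles the point. The check is whether the sections, read together, keep the recruiter from knowing the assignment and keep baseline ahead of it.

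1. **Who recruits?** Enumerators and dietitians (section 7.12; Informed consent). The dietitians deliver the intervention.
2. **Who assigns?** A data enumerator (Limitations). The students trained in patient selection are also trained in randomisation (Data collation phase) and work as enumerators (Budget).
3. **Who measures?** Enumerators (section 7.10; Data collation phase). Steps 1 to 3 therefore meet in one role.
4. **Is the sequence kept from that role?** Section 7.12 is headed as the place for the randomisation process and blinding. It names a source of numbers but no one who generates or holds the list, no central release and no envelopes. No assessor unaware of the arm is named anywhere in the protocol.
5. **Is baseline fixed before assignment?** The Project summary places baseline data at enrolment. Section 7.12 treats a patient as enrolled once consent is signed, with assignment to follow. Neither says which of baseline and assignment comes first.
6. **Which outcomes are exposed, and how?**

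| Route | HbA1c, glucose, lipids (laboratory) | 24-hour recall, PAID, knowledge score, physical activity (interview) | Blood pressure, anthropometry (manual) |
|---|---|---|---|
| Selective enrolment | yes | yes | yes |
| Arm known when baseline is measured | measurement not affected | yes | yes |

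7. **Do other safeguards cover this?** Against interviewer bias, Biases and Limitations propose noting average interview length in each arm. The Data collation phase adds investigator supervision, at least 10% accompaniments and 20% back checks. These bear on the quality of data collection. None hides the next assignment.

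**The case against.** The strongest reply is that silence is not an open list. Section 7.12 runs from explanation through eligibility and consent to assignment. If each number is drawn only after consent, nobody has foreknowledge. This stands as a limit: the protocol does not say that recruiters hold the assignments, and a reader should not infer that it does. It does not remove the point. A draw made after consent by the same enumerator, with no independent record, can still be influenced, and nothing excludes a list held in advance.

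Other inferences are tempting but unsupported.

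- **The work plan puts allocation before baseline.** It marks "Finalization of intervention and usual care arms in target hospital" in February 2021, participants in March and baseline in April. Since participants are finalised after that row, it more plausibly means setting up the arms. Individual assignment in February would also clash with assignment after consent in section 7.12.
- **The questionnaire opens with study group, so the arm is known at baseline.** The form serves both baseline and end line, and study group also comes before the consent item. Field order is therefore not time order. The design figure is not available to settle the matter.
- **The stated method fails to give "equal allocation of participants between the intervention and control group/usual care arm".** That phrase can mean a 1:1 ratio, and computer-generated numbers can come from a blocked list. Imbalance would matter little in any case: a split of 83 and 73 keeps 4 × 83 × 73 / 156² = 24,236 / 24,336 = 99.6% of the efficiency of 78 and 78.
- **The same individuals do everything.** Section 7.10 describes a hired team of three graduates, whereas the Design phase and Budget name final-year students. The staffing text is inconsistent, so the overlap is established for the role rather than for named individuals. Limitations still gives assignment to a data enumerator.

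**Conclusion.** The point holds as a weakness in the stated procedure. Randomisation sits with a role that also approaches patients and measures them, and the protocol provides neither concealment nor a rule that baseline is complete before assignment. The assurance that this procedure minimises selection bias is therefore not secured.

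The consequences differ by route. Selective enrolment, if it occurred, could affect the primary HbA1c comparison and all other outcomes. Knowledge of the arm at baseline could distort change in the interview and manual measures. It would not distort the laboratory measurement of HbA1c, so it would be wrong to conclude that all change scores are biased.

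The magnitude cannot be derived from the document, and any assumed shift in HbA1c would be invention. The conclusion rests on reading enumerator as one role across sections, and on treating concealment as trial conduct that belongs in the protocol, so an unseen analysis plan would not be expected to supply it. The protocol should be changed before recruitment, because analysis cannot reliably correct the fault afterwards.

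**What to change.** - Remove randomisation from the enumerators' training and tasks in the Limitations section and the Data collation phase.
- In section 7.12, name an investigator who neither recruits nor measures to generate and hold the list, preferably in permuted blocks of varying size so that the next assignment is hard to predict.
- Release each assignment by phone, or in sequentially numbered, sealed, opaque envelopes, only after consent, eligibility and all baseline measurements are recorded.
- State in the work plan that individual assignment follows baseline, and reword the February row if it means setting up the arms.

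The cost is protocol wording and either envelopes or a phone call per patient, with no new staff provided an existing investigator can stay out of recruitment and measurement. The one practical constraint is that baseline, including the blood sample and interviews, must be finished before the patient learns the arm.

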## **7.3. Study population/Sampling frame**

The source of the population of the study in both intervention and control group will be known cases of T2DM and newly diagnosed cases of T2DM patients who are within 25-64 years of age group attending the OPD of the hospital.

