## **7.4. Study site and its justification**

The study will be conducted in Tribhuvan University Teaching Hospital (TUTH) in Kathmandu, Nepal where superspecialist services is available with high patients flow.

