## **7.7. Inclusion and Exclusion criteria**

**Inclusion Criteria:**

- Diagnosis of type 2 diabetes
- HbA1c>48 mmol/mol (6.5%) at time of diagnosis ^21^
- male or female aged ≥24-64 years and visited in OPD of target hospital
- Those who give consent to participate in our intervention study

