**Exclusion Criteria:**

- Those who are pregnant women, lactating women or planning to become pregnant during

the course of study.

- Those who are severely ill or more than two comorbidities
- Those who have any plan to migrate from the study area for at least 1 year
- HbA1c ≥93mmol/mol (10.5%)
- Those who are on insulin therapy

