In the second phase, all patients in the intervention arm will be provided an individualized diet plan to reinforce the concept of controlling the serving size of foods every month which will be lasted for 45-60 minutes. During the patient's visits to OPD, the dietitian will obtain daily nutrient intake by asking the patients to recall the foods and beverages consumed for the past 24 hours. Each participant will be given an individual basis diet plan within the limit of the acceptable macronutrient distribution range (AMDR) ^20^. Energy requirements will be prescribed by a dietitian for each participant based on the patient's height, weight, and physical activity level according to the guidelines of the American diabetic association (ADA)^26^. Energy distribution will be set in accordance with the limit of AMDR i.e. protein 10-35%, fat 20-35%, and carbohydrate 45-65%)^20^. This guideline will be developed for the Nepalese population based on the ADMR compositions includes the use of a food exchange portion in diabetic diet planning. One piece of food exchange portion is defined as one serving for every 80 kcal of a food product. Thus, a similar type of food exchange portion can be exchanged where the nutritional value is almost the same. The individual total energy required per day is calculated according to the individual weight and daily physical activity level using Harris-Benedict equations. Balanced diet for each patient will be planned and the total day's diet plan is distributed into five meal patterns such as breakfast, launch, snack, and dinner and a bedtime snack. In order to avoid excessive energy intake and assure a balanced diet, we emphasize moderate carbohydrates, moderate fat foods and consuming foods rich in fiber and micronutrients. Follow up will be done every month. All educational materials will be developed in English and then translated into Nepalese language.

Table 1 Content of Nutrition Education and Counseling Module for DIAM-D trial

| SN | Topic | Module |
| --- | --- | --- |
| 1 | Knowledge about diabetes mellitus | Basic concept of nature of diabetes, causes and risk factors, types, clinical features, insulin action, body response to food in diabetes and non-diabetes state and complication |
| 2 | Treatment of diabetes | Diet alone, diet and drugs or diet and insulin, exercise and their  role in treatment of diabetes |

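### The only guard against contamination is advice not to share with an undefined group, and nothing stops members of one household being randomised to opposite arms

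*Protocol*

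**What the plan says.** Both arms come from one site (section 7.4: "The study will be conducted in Tribhuvan University Teaching Hospital (TUTH) in Kathmandu, Nepal") and from one patient stream (section 7.3: "attending the OPD of the hospital"). Allocation is by individual: under section 7.12, "participants will be enrolled in either intervention or control groups randomly using computer generated random numbers".

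The Limitations section names the risk: "Also, the cross-contamination may occur between intervention and control arms". The next sentence is the only countermeasure in the protocol: "We will suggest the participants from the intervention arm not to share the provided information with the others to prevent cross contamination".

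The intervention is largely carried out at home. Section 7.11 states that "all patients in the intervention arm will be provided an individualized diet plan to reinforce the concept of controlling the serving size of foods". The same section spreads the day's plan over five meals and uses food exchanges, and its module table adds a brochure and a demonstration of serving sizes in household measures.

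Eligibility in section 7.7 is broad in age and sex ("male or female aged ≥24-64 years and visited in OPD of target hospital"). The exclusions cover matters such as pregnancy, comorbidity, insulin use and planned migration ("Those who have any plan to migrate from the study area for at least 1 year"). None concerns a relative or household member who is already enrolled.

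**The concern.** There are two gaps.

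1. **The advice does not say whom it covers.** It names neither control participants nor other patients, and it makes no exception for family. What participants are asked to keep to themselves is also what a household cook would need in order to follow the plan: meals, portions and exchanges. If a participant who does not cook took the advice broadly, the diet could be delivered less fully. The Limitations section already concedes that adherence cannot be secured for everyone.

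2. **The advice cannot close the shared-kitchen route.** Two people with type 2 diabetes in one household, such as spouses or a parent and adult child, could both be eligible and be randomised separately. A control who eats meals prepared to the other person's plan is exposed even if nobody passes on any information.

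The first gap weakens the intervention arm and the second improves the control arm. If the intervention works, both shrink the between-arm differences in HbA1c, diet and knowledge.

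**Working it through.** **Text check.** Four places could hold a safeguard.

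| Place in protocol | What it contains | Household or contamination rule? |
|---|---|---|
| Limitations of the study | Advice not to share | Yes, but the group is undefined |
| 7.7 Inclusion and exclusion | Age, HbA1c, pregnancy, comorbidity, migration, insulin | None |
| 7.12 Randomisation | Individual allocation by computer-generated numbers | None |
| Questionnaire, baseline/end line | 24-hour recall, distress, knowledge, dietary adherence, physical activity | No item on exposure to trial materials or to a dietitian outside the trial |

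The monthly checklist in section 7.10 covers food, activity, adherence and complications, and does not name contamination. The sample size section allows for non-response and loss but not for contamination.

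**The plan's own sample size.** Inputs from the sample size section: Zα = 1.96, Zβ = 1.282, d = 0.64 (absolute value), S = 0.1, result 54 per arm.

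n per arm = 2 × (Zα + Zβ)² × S² / d²

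- With the printed S = 0.1: 2 × 3.242² × 0.01 / 0.4096 = 0.51, so 1 per arm. The printed inputs do not give 54.
- SD implied by 54 per arm: 0.64 × √27 / 3.242 = 1.026.
- With S = 1.0: 2 × 3.242² × 1 / 0.4096 = 51.3, so 52 per arm.

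An SD of about 1.0 is therefore used below. The printed S is a separate matter.

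**Illustration of dilution.** Assumptions not in the documents: SD 1.0, and a share c of controls who gain the full intervention effect by any route. The difference becomes 0.64 × (1 − c). With 54 per arm, SE = 1.0 × √(2/54) = 0.192, and power = Φ(difference/SE − 1.96).

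| c | Difference | Power, SD 1.0 | Power, SD 1.026 |
|---|---|---|---|
| 0% | 0.640 | Φ(1.37) = 91% | 90% |
| 10% | 0.576 | Φ(1.03) = 85% | 83% |
| 20% | 0.512 | Φ(0.70) = 76% | 74% |

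The arithmetic is the same if a share c of intervention patients gains none of the effect.

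**Could household pairs alone reach those shares?** Under independent 1:1 allocation, about half of all pairs fall in opposite arms, and each such pair contributes one exposed control.

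- c = 10%: 0.10 × 78 ≈ 8 controls, so about 16 pairs, or 32 of 156 participants (about 20%).
- c = 20%: 0.20 × 78 ≈ 16 controls, so about 31 pairs, or 62 of 156 participants (about 40%).

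Nothing in the documents suggests that much co-enrolment. The power table therefore describes contamination in general and does not estimate the household route.

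**The case against.** **The family reading is not the natural one.** The preceding sentence concerns contamination between the arms, and the advice gives that as its purpose. In that setting 'the others' most naturally means people in the other arm. The protocol also only suggests. A reader might infer that it forbids telling the person who cooks, so that the plan cannot be followed at home. The documents do not support that: no passage says so, and none says who cooks. What stands is that the phrase is undefined and can be misread. More precise wording may exist in the training or data-collection manuals, which are not shown, but an enrolment limit belongs in section 7.7.

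**The power loss is not a forecast.** A reader might infer from the table that power will fall to 76–85%. The shares are assumptions. They require exposed controls to gain the full effect without counselling, an individual plan or monthly follow-up, and household pairs alone are unlikely to reach them. This objection stands in full, and the figures are illustrative only.

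**Contamination would leave some trace.** A reader might infer that a null result could not be told apart from contamination. That is too strong. The baseline/end-line form holds a 24-hour recall, a knowledge questionnaire and a dietary adherence questionnaire. Improvement among controls, or flat adherence in the intervention arm, would be an indirect signal. A direct exposure item would be sharper but is an enhancement.

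**Naming contamination as a limitation is reasonable in a single-site, individually randomised trial.** Agreed. It does not explain leaving open a route that one eligibility line would close.

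**Conclusion.** The point holds as a modest, inexpensive improvement. The sole guard is advice addressed to an undefined group. It probably means control participants, but it could be taken to include household members whose help the diet plan may need. It cannot prevent exposure through shared meals, and neither eligibility nor randomisation stops two members of a household entering opposite arms. If the intervention works, both gaps bias the HbA1c, diet and knowledge differences towards zero.

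The size of that bias cannot be estimated, because the documents say neither who prepares food nor how often relatives would both enrol. The household route may involve few people.

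**What to change.** 1. In the Limitations section, and in any participant script that repeats it, reword the advice so that it asks intervention participants not to pass trial information or materials to other trial or clinic patients. State that it does not restrict sharing with household members who prepare food.
2. In section 7.7, add that only one person per household may be enrolled, and add a matching line to the screening checklist.
3. Optionally, add a short end-line item in both arms asking whether the participant received or saw trial materials from another patient, or saw a dietitian outside the trial. Report the answers by arm.

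The cost is a sentence of rewording, one eligibility line and, if wanted, one short questionnaire item. The downside is that a few second household members are not enrolled. The sample size and the primary outcome do not change.
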